**2.6. Significance of the study**

South Africa is undergoing a rapid transition from a diet high in fibre rich carbohydrates to a diet high in fat, animal-source foods, sugar and other refined (low fibre) carbohydrates. with the existence of multiple diseases such as chronic diseases and micronutrients deficiencies. Several studies have observed low consumption of micronutrients (iron and zinc) rich foods among children. Promotion and consumption of underutilized or forgotten crops (seeds) will help address the deficiency of these micronutrients, as it is both a short and long-term strategy. This research will help communities, especially in rural areas, to understand the significance of consuming these seeds, rather than discarding them as waste or storage for future cultivation. The current South African Food Based Dietary Guidelines for children between the ages of 3 to 5 years encourage feeding children regular, small meals and healthy snacks. The *Cucurbita Moschata* seeds can be eaten raw or roasted as a snack (Karanja *et al*., 2013). Many communities have access to these seeds, which are rich in minerals, vitamins, phytochemicals and antioxidants. This study seeks to develop a model to promote this underutilized or forgotten crop (seeds) and encourage communities to include these seeds in their daily meal as a snack. It is important to conduct this study to promote the value of this seeds.

1. **METHODOLOGY**

**3.1. Study design**

The study will use mixed methods depending on the phase of the study. This will include experimental, observation, qualitative, cross-sectional survey and a pretest-posttest control group trial. The designs are explained in detail under each phase, see figure below for sequencing of the phases.

**Figure 2: An illustration of the methodological sequencing of the phases**

**3.2. Target population:**

Preschool children, aged 3-5 years, in the Vhembe district of South Africa will be the participants in this study. This target group was selected because children under five years constitute the most vulnerable group of community and their nutritional status is a sensitive indicator of community health and nutrition (Ibeanu *et al.,* 2012). Furthermore, pre-school children are at an important stage of life where nutrition plays an important role in growth and development and has long lasting effects on health in later life (Khan Khattak and Ali, 2010).

**3.3. Location of study:**

The study will be conducted at registered government preschools in the Vhembe district of Limpopo province in South Africa. Vhembe district is one of five districts of Limpopo province, and is divided into four municipalities namely Musina**,** Thulamela**,** Makhado and Collins Chabane (Lim 345). The Vhembe district has a total population of 1,294,722, with 703,226 (53.3%) females and 591,496 (46.7%) males, 1*14* 984 (12.7%) children under five years. Furthermore, 67.2% of this population speaks *Tshivenda,* 24.8% *Xitsonga*, 1.3% Afrikaans, and 1.6% *Sesotho sa Leboa*. The District has very high unemployment rate of almost 24% (Stats SA, 2011). The total number of pre-schools (ECDs) registered under Department of Social Development in the government are 730 in 2018. The total number of children in preschools around the Vhembe district is 40291 (Department of Social Development, 2018). The researcher, [name] *et al*. (2015) previously reported 42.6% zinc prevalence and 28% iron prevalence in preschools in Vhembe district.

**3.4. Sampling**

Musina municipality will be purposefully selected from Vhembe District. These are in geographic proximity of the University of Venda where researcher is located and where the previous study was conducted ([name] *et al*., 2015). Simple random sampling will be used to select six preschools, three each from the two local municipalities. Simple random sampling is a sampling procedure, which provides equal opportunity of selection for each element in a population (Lee and Nieman, 2010). A list of pre-schools will be obtained from the Department of Social Development in Vhembe district and each pre-school will be assigned a number. The researcher will randomly select one number at a time. The following Slovin formula is used to calculate the total sample size used in the study: n = N/ (1 + (N X e^2^)) where

n= sample size

N= total number of children in the pre-schools; and

e = the accepted level of error

n = N/ (1 + (N X e^2^))

=40291/ (1+(40291 x 0.05)

=40291/ 101.7275.

= 396

= plus 10%

= 435.6

= 436

The formula yielded 396 participants, and an additional 10% will be added to account for attrition, making 436. Total sample size was calculated from the total number of children registered in the Early Childhood Development under Social Development in South Africa in 2017 in Vhembe district (Government Gazette, 2017). The sample frame will be six preschools, which are yet to be randomly selected. If the total number of participants in these six selected preschools does not reach the total number of 436, two more preschools will be added to the sample frame. The six preschools will be randomly assigned to the treatment or control.

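### The trial's size rests on a one-proportion survey formula, so its 5% error does not describe the between-arm comparison of randomised preschools

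*Protocol*

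**What the plan says.** Section 3.4 (Sampling) gives the only sample-size justification in the protocol: "The following Slovin formula is used to calculate the total sample size used in the study". The inputs are the preschool population, given in section 3.3 as "The total number of children in preschools around the Vhembe district is 40291", and "e = the accepted level of error", entered as 0.05. The result is carried forward: "The formula yielded 396 participants, and an additional 10% will be added to account for attrition, making 436".

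The same section then says: "The six preschools will be randomly assigned to the treatment or control". If 436 children are not reached, "two more preschools will be added to the sample frame". The schematic of the feeding trial in section 3.6.3 already lists eight preschools of 73 children, four per arm.

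Section 2.3 makes efficacy the primary aim and description of nutritional, zinc and iron status the secondary aim. Section 3.6.3.3 places randomisation at preschool level. Section 3.6.4.4 plans regression and ANOVA for change from baseline and for experimental against control.

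**The concern.** The formula answers a survey question: how many children, drawn individually at random, are needed to estimate one proportion to within e. The trial's main question is different. It compares two arms, and the units sampled and randomised are preschools, from two purposefully chosen municipalities. Nothing in the calculation refers to an arm, a difference to detect, a standard deviation, power or the correlation between children in one preschool.

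What is at stake is how the result will be read. If 436 is taken to mean that the comparison was sized for a 5% error, a difference that is not significant could be read as evidence that the seeds do not work, when the design may have been able to show only large differences. This is not something left to an analysis plan: the protocol itself fixes the size, and fixes it on a basis that does not fit its primary aim.

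**Working it through.** **Reproducing the protocol's figure.** n = N/(1 + N·e²) = 40291/(1 + 40291 × 0.0025) = 40291/101.7275 = 396.07, so 396. Then 396 × 1.10 = 435.6, so 436. The worked line prints "40291/ (1+(40291 x 0.05" without the square, but the next line, "40291/ 101.7275", shows that the square was used. The slip does not affect the result.

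**What 396 delivers under the formula's own conditions.** For one proportion at p = 0.5, simple random sampling: 1.96 × √(0.25/396) = ±4.9 points.

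**The same children split into two arms, still without clustering.** At the 42.6% zinc deficiency of section 3.3, with 198 per arm: 1.96 × √(2 × 0.426 × 0.574/198) = ±9.7 points. This is about twice the nominal 5, and it needs no assumption about clustering.

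**Adding the preschools.** Inputs from the protocol: 42.6% prevalence and six or eight preschools. Analysed children per preschool: 396/6 = 66; 73 enrolled less 10% is 65.7, so 66 also serves for eight. Assumptions, because the protocol gives none: ICC 0, 0.01, 0.05 and 0.10; two-sided 5%; 80% power; t distribution with (preschools − 2) degrees of freedom; no adjustment for baseline.

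Design effect DE = 1 + 65 × ICC = 1, 1.65, 4.25, 7.50.

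- Six preschools, 198 per arm, 4 df. Margin = 2.776 × √(2 × 0.426 × 0.574 × DE/198). Detectable difference in SD = (2.776 + 0.941) × √(2 × DE/198).
- Eight preschools, 264 per arm, 6 df. Margin = 2.447 × √(2 × 0.426 × 0.574 × DE/264). Detectable difference in SD = (2.447 + 0.906) × √(2 × DE/264).
- Overall survey margin, six preschools, normal approximation, p = 0.5: 1.96 × √(0.25 × DE/396).

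| Assumed ICC | 0 | 0.01 | 0.05 | 0.10 |
|---|---|---|---|---|
| Between-arm margin, six (points) | ±13.8 | ±17.7 | ±28.4 | ±37.8 |
| Between-arm margin, eight (points) | ±10.5 | ±13.5 | ±21.7 | ±28.8 |
| Detectable mean difference, six (SD) | 0.37 | 0.48 | 0.77 | 1.02 |
| Detectable mean difference, eight (SD) | 0.29 | 0.37 | 0.60 | 0.80 |
| Overall survey margin, six (points) | ±4.9 | ±6.3 | ±10.2 | ±13.5 |

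The rows for eight preschools use 8 × 66 = 528 analysed children. If the total stays at 396 analysed, spread over eight preschools (49.5 each), the between-arm margins with 6 df are ±12.2, 14.8, 22.5 and 29.4 points.

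**Attrition.** 436 × 0.90 = 392.4, against a target of 396; 396/0.90 = 440. The gap is four children, and 436 still keeps 396 if loss is at most (436 − 396)/436 = 9.2%.

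**The case against.** Several points on the other side are sound.

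- The arithmetic is right: 396 and 436 reproduce. The objection is to the choice of formula, not to the calculation.
- A reader might infer that the 0.05 is true of nothing the study reports. The protocol does not support that. Describing zinc and iron status is a stated secondary aim with its own cross-sectional phase, and ±4.9 points is correct for it if children within a preschool are uncorrelated.
- A reader might also infer that the protocol claims 5% precision for its results. It does not; 0.05 appears only as an input to the formula.
- Every clustered figure rests on an assumed ICC. The detectable differences also ignore baseline values, which a pretest-posttest trial can use to gain precision, so with adjustment they could be smaller.
- Six preschools is not the only reading. Eight appear in the schematic, and they narrow the margins by roughly a quarter.
- The protocol adds 10% for attrition, as it says it will. It does not say that 10% will be lost or that 396 must remain, so the gap of four children is a side remark.

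None of this reaches the central point. The primary aim is a contrast between arms, and for that contrast the formula's 5 points are missed with six or with eight preschools, and even at an ICC of zero.

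**Conclusion.** The point holds for the primary comparison. The stated basis for the trial's size is a one-proportion margin, and the between-arm difference in zinc deficiency is about twice as imprecise (±9.7 points) before any allowance for clustering or for the small number of preschools. With both allowances the margin is ±13.8 to ±37.8 points with six preschools and ±10.5 to ±28.8 with eight, for ICC 0 to 0.10. Detectable mean differences run from about 0.37 to 1.02 SD and from 0.29 to 0.80 SD respectively. These ranges depend on the assumed ICC, 66 analysed children per preschool, 80% power and no baseline adjustment.

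For the descriptive survey, the 5 points survive only without clustering.

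A reader might go further and conclude that the trial is underpowered. The protocol gives no target difference, standard deviation or ICC, so that cannot be shown. What can be shown is that the formula supplies no evidence either way. Nor does the protocol say that 436 was set by feasibility; it presents the number as the formula's result and provides for adding preschools to reach it.

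**What to change.** In section 3.4:

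1. Stop using the Slovin formula and its 5% error as the justification for the trial's size. If it is kept, limit it to the descriptive baseline survey and add a design effect.
2. Reconcile six preschools (section 3.4) with eight (the schematic in section 3.6.3), and the total number of children with them.
3. For the final number of preschools, state the detectable between-arm difference in serum zinc and haemoglobin, or the margin for deficiency prevalence. Give it over a stated ICC range, with degrees of freedom based on the number of preschools, and show any gain expected from baseline adjustment.
4. As a minor note, if the added 10% is the expected loss, say that 436 leaves about 392 children.

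The cost is one rewritten paragraph and a short calculation. The drawback is that the stated precision becomes less favourable, and the authors may then have to consider whether the number of preschools is enough.

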***Visit 1:***

A list of pre-schools will be obtained from the district office and preschools from Musina and Collins Chabane will be randomly selected. The selected preschools will be visited, and the research aims, and objectives will be explained to the headmaster. In addition, permission to include pre-schools in the sample will be requested.

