***Transferrin saturation***

TRFN reagent is used to measure the TRFN concentration by a turbidimetric method.1,2 In the reaction, TRFN combines with specific antibody to form insoluble antigen-antibody complexes. The SYNCHRON® System(s) automatically dilutes sample and dispenses the appropriate sample and reagent volumes into a cuvette. The ratio used is one-part diluted sample to 37.5 parts reagent. The system monitors the change in absorbance at 340 nanometers. This change in absorbance is proportional to the concentration of transferrin in the sample and is used by the System to calculate and express the transferrin concentration based upon a single-point calibration.

1. ***Tools and specific procedures: Record sheet.***

Data will be collected using a record information sheet for demographic data, environmental parameters, recent food intake, dietary intake, anthropometrics, and biochemical parameters. The record sheet will be developed, and pilot tested to check for anything that could impede the instrument's ability to collect data in economical and systematic fashion.

1. ***Validity and Reliability***

The validity of a measurement instrument is the extent to which the instrument measures what it is supposed to measure. Furthermore, reliability is the consistency with which a measuring instrument yields results with repeated measurements, preferably more than 10 repeats. Both validity and reliability, then, reflect the degree to which we may have errors in our measurements (Leedy and Ormrod, 2010). To ensure validity, the measurements for anthropometry will be taken twice and the average will be calculated, and the developed questionnaire and intervention will be piloted and pre-tested before data collection.

To ensure reliability, the developed questionnaire and educational lesson (the song) will be translated into *Tshivenda* and *Xitsonga*, which are the local language spoken in Musina and Collins Chabane municipalities. Experts from the MER Centre for African languages at the University of Venda will carry this exercise. One expert will translate the questionnaire from English to *Tshivenda* and *Xitsonga* and another expert from the same department will translate the *Tshivenda* and *Xitsonga* version of the questionnaire back to English.

1. ***Data analysis***

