**3.6.3.2. Objectives**:

3.6.3.2.1. To feed the children with the intervention or control for six months

- - - - 1. To assess adherence to the dietary intervention in terms of consuming Cucurbita *moschata* seed paste

**3.6.3.3. Design:** Study design will be a pretest-posttest control group trial, using cluster randomisation, which is a type of scientific experiment, which aims to reduce bias when testing a new treatment (Leedy and Ormrod, 2010). The preschools participating in the trial are randomly allocated either to the group receiving the treatment under investigation or to a group receiving standard treatment (or placebo treatment) as the control (Leedy and Ormrod, 2010). Randomized minimizes selection bias and the different comparison groups allow the researchers to determine any effects of the treatment when compared with the no treatment (control) group, while other variables are kept constant (Leedy and Ormrod, 2010). Randomization will take place at the preschool level. The research will be using single blinded trial with a knowledge of who is receiving the treatment amongst the participants.

- - - 1. **Intervention and data collection:**

The experimental group will receive their normal diet plus paste (grounded *Cucurbita moschata* seeds mixed with cooked *Cucurbita moschata* flesh) and the educational lesson through the song for six (6) months while the control group will receive normal diet plus mashed *Cucurbita moschata* flesh. The participants will consume ½ cup (64 g) (***to be confirmed after development and pilot***) paste (grinded *Cucurbita moschata* seeds mixed with mash *Cucurbita moschata* flesh) twice per week, during lunch with their normal diet while the control will consume mashed *Cucurbita moschata* flesh at the preschool sites over a six (6) month period. Two dishes made from grinded *Cucurbita moschata* seeds mixed with *Cucurbita moschata flesh* will be used to bring variety and improve compliance.

Grounded *Cucurbita moschata seeds* will be packaged at the food science laboratory at the university of Venda before being delivered to preschools. The packaged grounded *Cucurbita moschata seeds will be mixed with cooked Cucurbita moschata flesh at the preschool site. Mashed Cucurbita moschata flesh mixed with grinded seeds and Mashed Cucurbita moschata flesh* will be served to children during their lunchtime under the supervision of the researcher and trained field worker.

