**Table 3.3: Schematic representation of the feeding trial.**

| **Group** |  | **Estimated no** | **Intervention** | **Intervention days (three teams)** | **Quality control** |
| --- | --- | --- | --- | --- | --- |
| Experimental | Preschool 1 | 73 | Normal diet plus seed paste.  Song | Monday  Wednesday | Plate wastage observations and adherence recording |
|  | Preschool 2 | 73 | Normal diet plus seed paste  Song | Tuesday  Thursday | Plate wastage observations and adherence recording |
|  | Preschool 3 | 73 | Normal diet plus seed paste  Song | Monday  Thursday | Plate wastage observations and adherence recording |
|  | Preschool 4 | 73 | Normal diet plus seed paste  Song | Wednesday  Friday | Plate wastage observations and adherence recording |
| Control | Preschool 5 | 73 | Normal diet plus mashed butternut (placebo) | Monday  Wednesday | Plate wastage observations and adherence recording |
|  | Preschool 6 | 73 | Normal diet plus mashed butternut (placebo) | Tuesday  Thursday | Plate wastage observations and adherence recording |
|  | Preschool 7 | 73 | Normal diet plus mashed butternut (placebo) | Monday  Thursday | Plate wastage observations and adherence recording |
|  | Preschool 8 | 73 | Normal diet plus mashed butternut (placebo) | Wednesday  Friday | Plate wastage observations and adherence recording |

The intervention will be implemented over six months or 180 days. On intervention days, Monday to Thursday, the field workers and the researcher will be on site for quality control. They will work in teams of two, one team per preschool. The researcher will change team daily to ensure standardisation and quality control**.**

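### Preschools are sampled from two municipalities, but their assignment to arms is not restricted by municipality, so arm can coincide with municipality by chance

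*Protocol*

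**What the plan says.** Section 3.4 makes municipality a sampling stratum: "Simple random sampling will be used to select six preschools, three each from the two local municipalities". The same section names only one of the two: "Musina municipality will be purposefully selected from Vhembe District". The other appears under Visit 1 in section 3.6.2.4 ("preschools from Musina and Collins Chabane will be randomly selected") and again in the validity and reliability paragraph of section 3.6.2.5.

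On allocation, section 3.4 has one sentence: "The six preschools will be randomly assigned to the treatment or control". Section 3.6.3.3 calls the design cluster randomised and adds: "Randomization will take place at the preschool level". Neither place gives an allocation ratio, or any stratum, block or matching.

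If the six preschools hold too few children, "two more preschools will be added to the sample frame"; which municipality they come from is not said. The feeding-trial schematic in section 3.6.3 already lists eight preschools, four per arm, with no column for municipality. Section 3.6.4.4 and Table 3.5 compare the arms by regression and ANOVA and name no municipality term.

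**The concern.** The plan balances municipality when it samples and then drops it when it allocates. With six or eight units, chance alone can place most or all preschools of one municipality in the same arm. Municipalities may differ in baseline zinc and iron status, in home diet and in exposure to infection, and the last two may also change differently over the six months of feeding. Under complete alignment, municipality and arm are the same variable, and no model can tell a municipality effect from a seed effect. Under partial alignment, the unadjusted arm difference carries a fraction of the municipality difference. The question has to be settled before allocation, because complete alignment cannot be undone afterwards.

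**Working it through.** **Inputs.** Six preschools, three per municipality, and two more as a contingency (section 3.4). Four preschools per arm when eight are used (feeding-trial schematic, section 3.6.3). Assignment at random by preschool with no stated restriction (sections 3.4 and 3.6.3.3). The plan gives no figure for municipality balance, so there is none to reproduce. A 3:3 split of six preschools and a 4+4 origin of eight are assumptions, so alternatives are shown.

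**Six preschools (3+3), split 3:3.** There are C(6,3) = 20 allocations. The number with k preschools of one municipality in the treatment arm is C(3,k) × C(3,3−k):

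- k = 0, 1, 2, 3 gives 1, 9, 9, 1 allocations.
- Complete alignment: (1 + 1)/20 = 10%.
- 2:1 in one municipality and 1:2 in the other: 18/20 = 90%.
- Exact balance is impossible, because three is odd.

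**Six preschools, independent coin flips.** There are 2^6 = 64 assignments. Complete alignment: 2/64 = 3.1%. A further 2/64 = 3.1% put all six in one arm.

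**Eight preschools (4+4), split 4:4.** There are C(8,4) = 70 allocations:

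- Complete alignment: 2/70 = 2.9%.
- 3:1 splits: 2 × C(4,3) × C(4,1) = 32, and 32/70 = 45.7%.
- 2:2 balance: C(4,2)² = 36, and 36/70 = 51.4%.

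**Eight preschools, both extra ones from the same municipality (5+3), split 4:4.** Complete alignment is impossible. All three preschools of the smaller municipality fall in one arm in C(5,1) + C(5,4) = 10 of 70 allocations, or 14.3%.

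**Share of the municipality difference carried into the unadjusted arm difference** (preschools weighted equally). Complete alignment: 1. A 3:1 split: 3/4 − 1/4 = 1/2. A 2:1 split: 2/3 − 1/3 = 1/3. The average absolute share without restriction is 0.10 × 1 + 0.90 × 1/3 = 0.40 for 3+3, and (2/70) × 1 + (32/70) × 1/2 = 0.26 for 4+4.

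**After assigning within municipality.** For 3+3, the chance of complete alignment falls from 10% to 0, but every allocation is 2:1 against 1:2, so the share is fixed at 1/3 (from 0.40 on average). For 4+4, every allocation is 2:2 and the share is 0.

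**Price of a municipality term.** At cluster level with six preschools, residual degrees of freedom go from 6 − 2 = 4 to 3. The two-sided 5% critical t goes from 2.776 to 3.182, and 3.182/2.776 = 1.15. Intervals are therefore about 15% wider from the critical value alone, unless municipality explains enough variance to offset it.

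**The case against.** The strongest reply is that the protocol is silent rather than wrong. It describes the sampling as simple random, but for allocation it says only that assignment is random. A reader might infer that simple, unrestricted randomisation is prescribed. The text does not say so, and a randomisation plan could add the restriction. This stands as a correction of wording. It does not remove the point, which needs only that no restriction is stated anywhere.

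A reader might also take 10% as the risk. That figure needs a fixed 3:3 split, which section 3.4 does not give; under coin flips or the tabulated 4:4 the risk is about 3%. For six preschools the remedy is modest, since 18 of the 20 unrestricted 3:3 allocations already have the 2:1 pattern that the restricted scheme produces. Both of these stand.

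It might further be inferred that the two municipalities are known to differ. The documents do not support this. Section 3.3 gives zinc and iron prevalence for the district only. The language passage names Tshivenda and Xitsonga for the two municipalities jointly ("which are the local language spoken in Musina and Collins Chabane municipalities") and does not assign one to each.

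Finally, baseline status is measured, change from baseline is analysed (section 3.6.4.4), all children are dewormed (section 3.6.2.5), and home diet is recorded by diary (section 3.6.3.5). Measured baseline differences can therefore be addressed. What remains under complete alignment is any unmeasured municipality effect, including a different course over the six months.

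**Conclusion.** The point holds as an inexpensive design improvement. As written, the plan allows arm and municipality to coincide, with probability 10% (six preschools, 3:3), 3.1% (six, coin flips) or 2.9% (eight, 4+4, split 4:4). With eight preschools, close to half of the unrestricted allocations (34/70 = 48.6%) are unbalanced.

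It would go too far to call the comparison biased. The imbalance arises by chance and averages out over repeated randomisations; the harm is to the one trial actually run. Nor can the damage be sized, because the documents give no municipality effect on zinc or iron. What is certain is that under complete alignment such an effect, if present, could not be separated from the seed effect. The probabilities rest on the stated allocation ratios and, for eight preschools, on four coming from each municipality.

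**What to change.** In section 3.4, name both municipalities (Musina and Collins Chabane) and state: *Preschools are randomly assigned to arms within municipality.* Then, according to the number of preschools:

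- **Eight, as in the feeding-trial schematic:** sample four per municipality, taking one of the two added preschools from each, and allocate 2:2 in each. Balance is then certain instead of 51%.
- **Six:** allocate 2:1 in one municipality and 1:2 in the other, choosing at random which gets which. This removes complete alignment and leaves the 2:1 imbalance.

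Sections 3.4 and 3.6.3 also need to agree on whether six or eight preschools are planned, since the scheme depends on it.

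The cost is a sentence or two in section 3.4 and a short allocation list, with no preschool beyond the eight the protocol already foresees. A municipality term in the analysis is optional. With six preschools it takes one of four cluster-level degrees of freedom, with the loss of precision shown above, so the choice should be made in advance.

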**3.6.2. PHASE TWO: BASELINE SURVEY.**

**3.6.2.1. Aim:** The aim will be to recruit, and screen potential participants and collect baseline data.

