***Visit 2:***

A parents’ meeting will be arranged. The researcher will provide explanation to parents who need clarity before giving consent for children to participate in the study. A list of children whose parents will consent will be generated.

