Promotion of the consumption of the seeds and nutrition education will be done in the form of a song, which is known to be the best method for educating children under the age of five years. The training on the consumption of the seeds will involve the guardian/parents during participant’s recruitment because children at this age are still fully dependent for food on their caregivers/parents who thus influence their eating habits (Curtis *et al*., 2011). The focus of the training will be on the health benefits of consuming seeds of *Cucurbita* *spp.* The songs will be easily learned by preschool children and will become favourites because of their familiarity. Furthermore, the songs will build confidence in preschool children and even shy children are likely to participate as part of a group or whole class. The recorded lyrics during the Pilot will be used. The table below is a schematic representation of the feeding trial.

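### Parents are to be trained on the seeds during recruitment, with the time of allocation left open, so either the arm is disclosed during enrolment or control parents receive seed promotion

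*Protocol*

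**What the plan says.** **Allocation.** Protocol section 3.4 (Sampling) states: "The six preschools will be randomly assigned to the treatment or control". The Phase Three design (3.6.3.3) confirms the unit, "Randomization will take place at the preschool level", and describes allocation of the participating preschools a second time. Neither place says whether allocation comes before or after consent and baseline.

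**Recruitment, consent and baseline.** These belong to Phase Two, whose aim reads: "The aim will be to recruit, and screen potential participants and collect baseline data". Section 3.6.2.4 puts four visits under recruitment. Visit 1 is to the headmaster. Visit 2 is a parents' meeting, after which "A list of children whose parents will consent will be generated". Visits 3 and 4 are for data collection.

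**Parent training.** The intervention text under 3.6.3 states: "The training on the consumption of the seeds will involve the guardian/parents during participant’s recruitment". On content it says: "The focus of the training will be on the health benefits of consuming seeds of" *Cucurbita* species. It does not say which preschools' parents attend.

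**Education by arm.** The same section gives the seed paste and the song lesson to the experimental group and mashed flesh to the control group. The schematic table of the feeding trial lists the song for experimental preschools only.

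**The concern.** In a cluster trial, randomising the preschools balances the preschools that are drawn. It does not balance the families who agree to join once they know, or can guess, what their preschool will receive. If the arm becomes visible during enrolment, the two arms may enrol different kinds of family.

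If the training goes to control parents instead, the contrast shrinks. Section 3.6.3 justifies the training by saying that caregivers determine what young children eat. Section 2.6 says many communities have access to the seeds, and section 1.7 says the crop is grown locally and its seeds are thrown away. A control family persuaded of the benefits could therefore act on it at home. Section 2.5 also expects eating patterns to improve through nutrition education, and that comparison would be weakened too.

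There are few clusters: three per arm if six preschools are split evenly, or four per arm in the schematic table. Adjusting afterwards for either problem would be unreliable.

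**Working it through.** No figure in the protocol belongs to this point, so the check sets the sections against each other and asks whether any order of steps avoids the problem.

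Two facts are fixed: training falls within recruitment, and recruitment contains consent. Two are not fixed: whether the allocation is known when the training is given, and which parents are trained.

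| Allocation known at training? | Parents trained | Consequence |
|---|---|---|
| Yes | Experimental preschools only | The arm is disclosed during recruitment, and before consent if training precedes the signature |
| Yes | All preschools | Control parents receive seed promotion |
| No (the Phase Three reading) | All preschools, since training cannot be specific to an arm | Control parents receive seed promotion |

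The fourth combination, allocation unknown but only experimental parents trained, is impossible. The three rows are therefore exhaustive, and none keeps both enrolment free of arm knowledge and control parents free of the promotion.

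**Baseline.** The food frequency questionnaire, which covers the seeds and has a line for roasted butternut seeds (3.6.2.5 and Appendix D), and the blood sample are taken in Phase Two. The only meeting called for parents is Visit 2, before data collection at Visits 3 and 4. Training given then would precede baseline diet and blood in whichever preschools received it. The protocol does not say that training happens at that meeting, so this is a possibility and not a stated step.

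**Added preschools.** Section 3.4 adds two preschools if the six do not reach 436 children, yet its assignment sentence covers only six. The schematic table shows eight. When and how the added two are allocated is not stated, which leaves the order of enrolment and allocation open for them as well.

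**The case against.** Three stronger readings are tempting, and the documents do not support them.

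- A reader might infer that preschools are assigned at the sampling stage, before anyone visits them. That rests only on where the sentence sits. Section 3.1 says designs are explained under each phase, and allocation is explained under Phase Three, after recruitment and baseline. The plan of action in 3.12 dates baseline to April 2021 and feeding to May 2021, which fits later allocation.
- A reader might infer that training takes place at the consent meeting, before parents sign. The text says only that it is during recruitment, and the account of Visit 2 does not mention training. Training after signature is compatible with the text.
- A reader might infer that control parents are told to feed seeds at home. The stated content is health benefits, with no such instruction.

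It can also be argued that the plan has safeguards. Zinc and iron status are measured at baseline, and 3.6.4.4 analyses changes from baseline. Home diet is followed by a weekly diary (3.6.3.5). Consent must in any case explain possible benefits to every parent (3.9).

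Much of this stands. If allocation does follow baseline, consent with the arm known disappears. But training at recruitment then reaches control parents, so the problem changes form and does not go away. Baseline values and diaries can reveal selection or contamination, and a change analysis can remove part of a baseline difference. They do not restore a diluted contrast, or make alike families who enrolled for different reasons. A consent explanation that mentions benefits is also less than training whose focus is those benefits.

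Figure 2 (phase sequencing) and the consent form in Appendix H were not in the text available here. A clear statement in either could narrow the point, but the training sentence would still need to change.

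**Conclusion.** The point holds in this form: the time of allocation relative to consent and baseline is not fixed, and training parents on the seeds during recruitment conflicts with an education component meant for the experimental arm. Whatever the order, the result is either disclosure of the arm during enrolment or seed promotion to control parents, possibly before baseline measurement.

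The conclusion rests on the training sentence in 3.6.3 meaning what it says about timing, and on recruitment being the Phase Two activity described in 3.6.2.4. It does not depend on allocation being early or on training preceding consent.

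No size can be given. The documents contain no refusal rate, no difference between consenting and declining families, and no rate of home seed use from which bias or dilution could be calculated. The mildest case the text allows is training of experimental parents only, after they have signed and after baseline in their preschool. Harm would then be small, but nothing in the protocol requires that sequence. The change should be made because it is cheap and removes both risks.

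**What to change.** 1. In the intervention text of 3.6.3, move parent training on the seeds to after consent, baseline and randomisation, and limit it to intervention preschools.
2. In 3.4 and 3.6.3.3, state that all preschools, including any added to reach the sample size, are randomised together once consent lists are closed and baseline is complete in every one of them.
3. In 3.6.2.4 (Visit 2), state that the same neutral explanation of the study is given to parents in both arms before consent.

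The cost is one later parents' meeting in the intervention preschools, and feeding cannot start anywhere until the last baseline is finished. Section 3.6.2.4 allows 20 days in total for the baseline visits, and 3.12 already places baseline in the month before feeding, so the order fits the existing timetable. The change must be made before recruitment begins.
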